## Methods

### Characteristics of the Research Population

#### Number of Subjects

We will enroll a maximum of 90 (aim 1: n=50, 30 patients, 20 service providers; aim 2: n=40) participants in the study. We expect that 1 in every 3 persons that we screen will enroll in the study; thus, we anticipate screening 140 individuals to reach our enrollment goal.

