#### Procedures

Using the Centers for Disease Control and Prevention guidance for emtricitabine/tenofovir (Truvada) for PrEP and/or the approved generic equivalent, we will identify prospective subjects through SMH FHT sites and community-based agencies. Staff will assess all black patients for PrEP eligibility and interest in initiating PrEP. We will purposively select subjects who want to start PrEP (n=10), do not want to start PrEP (n=10), and remain undecided (n=10) for one-on-one qualitative interviews. We will monitor sexual orientation to ensure MSM are represented in the sample. In the interviews, we will inquire about their (1) concerns about PrEP and barriers to PrEP initiation, (2) normative beliefs about PrEP, and (3) decision-making processes regarding PrEP use. We will also conduct surveys with SMH FHT staff and staff at community-based agencies who assess patient risks and make clinical recommendations for PrEP as well as those that may prescribe and/or support clinical PrEP management. We will use these qualitative findings to guide the adaptation of the ODSF for use in supporting the decisional needs of black patients who are considering PrEP. Patients will receive Can $30 (US $22) for completing the interviews. Providers will receive a Can $40 (US $29) gift card to Amazon on the web for filling in the survey tool as their participation will occur over the course of their work.

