#### Randomization

A block randomization strategy will be used to randomize patients in aim 2 into the experimental or control groups. Random blocks of 2, 4, and 6 are used.

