#### Patient Surveys

RAs will send participants an email with the link to access the web-based structured survey, which will be programmed in Snap Professional software. All data were entered into Snap Professional software. Once the survey is complete (ie, the submit button is selected), the survey is uploaded automatically to the Snap web host. As soon as this transfer is complete, the survey and its data are automatically removed from the device. We will collect whole blood using a finger-stick procedure and use the microfluid sample for dried blood spot analysis.

#### Measures for Aim 2

In addition to basic demographic data that will be used to describe the sample (eg, age, gender, relationship status), we will use the measures summarized below to assess key variables necessary to address aim 2:

The sure test indicates *the probability that a patient experiences clinically significant decisional conflict.*The stage of decision making is a 4-6 item instrument. *Stage of decision making refers to the individual’s readiness to engage in decision making, progress in making a choice, and receptivity to considering or re-considering options.*The Decisional Conflict Scale is a 16-item tool.* The Decisional Conflict Scale (DCS) measures personal perceptions of: (1) uncertainty in choosing options, (2) modifiable factors contributing to uncertainty such as feeling uninformed, unclear about personal values and unsupported in decision making; and (3) effective decision making (in full version) such as feeling the choice is informed, values-based, likely to be implemented and expressing satisfaction with the choice.*The Decision Preparation Scale is a 10-item scale. *The scale assesses a patient’s perception of how useful a decision aid or other decision support intervention is in preparing the respondent to communicate with their practitioner at a consultation visit and making a health decision.*The Health Care Climate Questionnaire (HCCQ) is a 15-item questionnaire. *The HCCQ was designed to be used by patients to report their perceptions of their doctors or their team of health care providers*The PrEP Self-Regulation Questionnaire is a 15-item questionnaire that elicits information regarding why an individual may initiate and/or maintain PrEP usage.The PrEP Use Perceived Competence Scale is a 4-item scale for individuals who elect to use PrEP regarding their perceived confidence to adhere to their decision to use PrEP.

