###### Aim 2: Analysis Plan

To compare conditions, we will use analysis of covariance procedures. When we compare the 4 conditions, our primary interest will be the tests of participants who received the decision-support intervention versus the information-only control. We will test whether the decision quality, PrEP initiation, and PrEP adherence differ between conditions controlling for baseline decision-quality score. We did not conduct a power analysis to calculate sample size because we de-emphasized hypothesis testing in favor of generating effect size estimates to inform the development of a larger study.

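### PrEP initiation is adjusted only for a baseline decision-quality score; baseline leaning toward or away from PrEP, a plausible strong predictor of starting, enters neither the randomisation nor the model

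*Protocol article*

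**What the plan says.** Under Aim 2: Analysis Plan the method is "To compare conditions, we will use analysis of covariance procedures", and the covariate is the same for every outcome: "We will test whether the decision quality, PrEP initiation, and PrEP adherence differ between conditions controlling for baseline decision-quality score". No definition of that score is given.

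Measures for Aim 2 lists the instruments. The Decisional Conflict Scale covers "uncertainty in choosing options, (2) modifiable factors contributing to uncertainty such as feeling uninformed, unclear about personal values and unsupported in decision making", together with how effective the choice feels. The stage-of-decision measure covers "readiness to engage in decision making, progress in making a choice, and receptivity to considering or re-considering options". The SURE test and the preparation scale concern clinically significant conflict and the usefulness of the aid. None is described as recording which option the person prefers.

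Randomization describes plain blocks: "Random blocks of 2, 4, and 6 are used". It states no stratification factor. Inclusion Criteria rely on the referring provider's view that the person is suited to start PrEP; the person's own wish is not a criterion.

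Aim 1 does record leaning. Its Procedures section says: "We will purposively select subjects who want to start PrEP (n=10), do not want to start PrEP (n=10), and remain undecided (n=10". Aim 2 (40 participants, per Number of Subjects) has no corresponding item in its measures, allocation or analysis.

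**The concern.** Adjusting the day-14 scale outcome for its own baseline is sound. For initiation, the covariate is poorly matched to the outcome. If the score reflects how settled a person is, someone firmly for PrEP and someone firmly against it can score alike, yet their chances of starting differ widely. The adjustment would then remove little of the outcome's variance.

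What is at stake is precision. The protocol gives up hypothesis testing in favour of effect sizes that will inform a larger study, so the quality of the initiation estimate is the product of aim 2. Leaning that is not recorded before allocation cannot be recovered later without contamination by the intervention.

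**Working it through.** **Inputs from the protocol.** Aim 2 has 40 participants in two arms. Equal allocation, about 20 per arm, is inferred from the block sizes. The protocol gives no initiation rate, no leaning mix and no power figure, so there is no stated figure to reproduce.

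**Assumptions.** The shares who want PrEP, are undecided, or do not want it, and the proportion starting in each group, are assumed and varied. There is no true treatment effect.

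**Variance explained.** For shares w and start rates p, the overall rate is m = Σwp, the total variance is T = m(1 − m), and the between-group variance is B = Σw(p − m)². Then R² = B/T.

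With equal thirds and 70/35/5%:
- m = (0.70 + 0.35 + 0.05)/3 = 0.3667, and T = 0.3667 × 0.6333 = 0.2322.
- B = (0.3333² + 0.0167² + 0.3167²)/3 = 0.0706, so R² = 0.0706/0.2322 = 0.304.
- Settled (want and do not want pooled: 37.5%) against undecided (35%) gives R² = 0.0006.

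**Chance imbalance.** The SD of the shift in the risk difference due to leaning alone is √(B × 2/20) = √(0.0706 × 0.1) = 0.084, or 8 percentage points. The unadjusted SE is about √(T × 2/20) = √(0.2322 × 0.1) = 0.152. The 8 points are already part of that SE.

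**Effect of adjustment.** Standard errors are from 20,000 simulated trials of 40, with leaning as a three-level covariate.

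| Mix (want : undecided : do not want) | Start rates | R² leaning | R² settledness | SE unadjusted | SE adjusted for leaning | Reduction |
|---|---|---|---|---|---|---|
| thirds | 70/35/5% | 0.304 | 0.0006 | 0.1531 | 0.1315 | 14% |
| thirds | 60/40/15% | 0.143 | 0.0006 | 0.1537 | 0.1457 | 5% |
| 50:40:10 | 70/35/5% | 0.197 | 0.056 | 0.1578 | 0.1468 | 7% |
| 50:40:10 | 60/40/20% | 0.07 | 0.017 | 0.1589 | 0.1575 | 0.9% |

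In the first row, adjusting for settledness instead gives 0.1553, no better than no adjustment. A repeat of that row with leaning as one ordered term gives about 0.130, a reduction of about 15%. The gain from 0.1531 to 0.1315 is worth 40 × (0.1531/0.1315)² ≈ 54 patients. The 95% half-width falls from 1.96 × 0.1531 = 0.30 to 1.96 × 0.1315 = 0.26.

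**A second set of assumptions**, with fixed mixes of 13/14/13 and 20/14/6 out of 40:
- Rates 0.8/0.4/0.1: the SE falls from 0.156–0.157 to 0.132–0.138. Leaning imbalance alone moves the risk difference by 10 points or more in 28–30% of trials.
- Rates 0.7/0.4/0.2: the SE falls from 0.157–0.160 to 0.147–0.150, and the 10-point shift occurs in 12–13% of trials.
- Rates 0.6/0.4/0.3: the SE is essentially unchanged, and the 10-point shift occurs in 1% of trials or fewer.
- Rates 0.9/0.5/0.05, a very steep gradient: the SE falls from 0.155–0.160 to 0.119–0.124, more than in any row of the table.

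**Sparse cells.** The chance that no one in the do-not-want group starts is (1 − w × p)^40. At 70/35/5% this is (1 − 0.0167)^40 = 0.51 with thirds and (1 − 0.005)^40 = 0.82 at 50:40:10. A logistic model with leaning as separate categories would often meet separation.

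**The case against.** The strongest reply is that nothing here is an error: allocation is randomised, the article is a condensed protocol, and omitting a prognostic covariate costs only efficiency. Much of that stands. A reader might infer that chance imbalance biases the initiation estimate. It does not; the imbalance is ordinary sampling error that a valid interval already carries. The covariate choice is nevertheless stated in the article rather than left open, so it can be reviewed as written.

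A reader might also infer that leaning is the strongest baseline predictor of starting. No passage says so or gives a figure. Aim 1's 10/10/10 quota is purposive sampling for interviews and does not establish prediction. Nor does the quota carry over to aim 2, where firm decliners could well be fewer.

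The claim that the planned covariate is blind to direction is likewise an inference. The score is undefined, the Decisional Conflict Scale also touches on whether a choice will be carried out, and the Self-Regulation Questionnaire asks why someone may initiate, though it is not named as a covariate. Even pure settledness is not always useless: it explains 5.6% of the variance at 50:40:10 with 70/35/5%.

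Finally, extending the point to drug levels is tempting, but no calculation supports it and H3 concerns initiators only. The point is confined to initiation.

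**Conclusion.** The concern holds as a matter of precision. For initiation, the plan fixes a covariate that, on the protocol's description of its measures, is not shown to capture which way a person leans, and leaning is handled nowhere else in aim 2. The SE of the risk difference would fall by under 1% to about 15% across the tabulated scenarios, more under a still steeper gradient, and adjustment for leaning did not raise the SE in any scenario tried. In absolute terms the pilot stays imprecise: the 95% half-width is about 30 points unadjusted and 26 in the 70/35/5% equal-thirds case.

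This rests on assumed mixes and start rates, equal arms, and reading the undefined score as a measure of certainty or readiness. It is worth acting on because the change is cheap and must be made before allocation. At the time of the article aim 2 had not begun.

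**What to change.** - Add aim 1's question (want to start, undecided, do not want to start) to the aim 2 baseline survey, answered before allocation.
- For the initiation contrast, prespecify leaning as a covariate, for example as one ordered term. Report the adjusted risk difference with its interval, using linear adjustment or another standardisation that tolerates cells with no starters.
- Define the decision-quality score and keep its baseline value as covariate for the day-14 scale outcome.
- Keep the baseline conflict grouping wherever the four conditions or H2 and H3 need it.

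The cost is one extra survey item and one or two degrees of freedom in a model for 40 people. If leaning turns out to predict starting only weakly, the gain will be small.

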###### Data Handling

The statistical analyses for the study will be performed at McMaster University by LM. Once all self-report surveys and biological data have been entered into Snap Professional software, LN will download a complete database with no identifying information and provide it to LM for analysis. No identifiable information was included in the downloaded database.

###### Data and Safety Monitoring

LN and [name] will review patient data biweekly, commencing 14 days after the first participant is enrolled in the trial of the decision support intervention. [name] will chair the patient safety review team. The research manager will prepare routine safety data reports for review by the research team. The study team will meet monthly or as needed throughout the study implementation to review safety data as well as discuss and address any potential safety concerns. The study team will agree on the content and format of safety data reports before study implementation. Furthermore, as this study does not have data safety monitoring board oversight, the SMH Institutional Review Board may also review aggregate⸺or individual level−safety data.

The data and safety monitoring responsibilities of the study team will include the following:

Maintain confidentiality of the data and results of the monitoring.Review the research protocol and plans for data safety and monitoring.Review monthly (or more frequently as needed).Participant recruitment:Retention between recruitment and data collectionParticipant risk-benefit ratioUnanticipated adverse effectsMonitor reports of related studies to determine if this study needs to be changed or terminated.Review proposed modifications to the study before implementation.Determine if the study should continue as designed, modified, or terminated based on the data available at the review meeting.

In addition to the routine safety data reviews, the study team will convene on an ad hoc basis to make decisions regarding the handling of any significant safety concerns. If necessary, experts external to the study representing expertise in the fields of community-based research, biostatistics, or medical ethics may be invited to join the safety review. A recommendation to stop the study may be made by the study team at any such time that the team agrees an unacceptable type and/or frequency of adverse events has been observed. In the unlikely event that the study team has serious safety concerns that lead to a decision to permanently discontinue the study for all participants and stop accrual into the study, the principal investigator will immediately notify the SMH Institutional Review Board.

## Results

A research award was funded on March 2017. Ethical approval was received on March 25, 2019 (with supplemental approval received on May 10, 2019). Data collection started on April 9, 2019. As of September 30, 2019, we enrolled 29 patients and 24 health care providers for aim 1. We are currently analyzing the data collected for aim 1. Aim 2 is scheduled to start in May 2020.

## Discussion

This study will provide evidence-based information on the decisional needs of black patients who are at risk of HIV and have been offered PrEP. The study will also test the effect of the decision support intervention in reducing decisional conflict, adoption of PrEP, and adherence to PrEP.

## Appendix

Multimedia Appendix 1 SON peer review letter.

Multimedia Appendix 2 Ottawa Decision Support Framework (ODSF).

## Abbreviations

ACB: African, Caribbean, and Canadian Black
C4: Client-Centered Care Coordination
CATIE: Canadian AIDS Treatment Information Exchange
GTA: Greater Toronto Area
HCCQ: Health Care Climate Questionnaire
HDC: high decisional conflict
LDC: low decisional conflict
MSM: men who have sex with men
ODSF: Ottawa Decision Support Framework
PrEP: pre-exposure prophylaxis
RA: research assistant
SDT: self-determination theory
SMH FHT: St Michael’s Hospital Family Health Team
SSL: secure socket layer
STI: sexually transmitted infection
